## 2. Materials and Methods

### 2.1. Study Design, Setting, and Sample Size

This is a single-center open-label two-arm randomized controlled crossover superiority trial (RCCT) adhering to CONSORT guidelines [39] with a total duration of 20 weeks (Supplementary Material). The study is conducted at the Swiss Paraplegic Research in Nottwil, Switzerland. It involves two 8-week interventions consisting of daily intake of either a probiotic (Biotics-G, Burgerstein AG, Rapperswil-Jona, Switzerland) or a prebiotic (Oat Bran, Naturaplan, manufactured by Swissmill, Zurich, Switzerland) supplement, separated by a 4-week washout period (Figure 1). Group allocation, which determines the order of supplement intake by the participants, is determined using a permuted block randomization (block size 4). For this, a randomization list was created using the statistical software Stata (Stata. Version 18. College Station, TX, USA: StataCorp, 2024). Due to the nature of the supplements, no allocation concealment or blinding of study personnel or participants is possible. Recruitment for this study started in summer 2025, and data collection will continue for two years; the study is therefore expected to end in summer 2027. The low-risk nature of this study warrants a risk-based approach for study monitoring. The study will be conducted in accordance with the Declaration of Helsinki. The study was approved by the Ethics Committee for Northwest/Central Switzerland (EKNZ, ID: 2025-00238, 24 February 2025, Version 2.0). The study is registered at ClinicalTrials.gov (ID: NCT06870331, 2 April 2025). Written informed consent will be obtained from all participants involved in the study.

The sample size was calculated for the primary outcome (changes in GIQLI) based on the results of a previous pilot study [34], applying a clinically relevant mean difference of 10 points on the GIQLI [40,41,42] and correcting for a larger expected variability in the GIQLI in the current study population. Assuming a significance level of 5% and a power of 85%, a sample size of 50 participants, with 25 participants in each group, was determined.

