### 2.2. Study Participants

Adult (≥18 years old) male and female individuals with chronic (>1 year) traumatic and non-traumatic SCI, with a complete or incomplete lesion according to the American Spinal Injury Association Impairment Scale (AIS A-D), are invited to participate. Individuals experiencing significant GI complaints, indicated with ‘yes’ at screening and a GIQLI score below 110 at baseline (T1), are included. Exclusion criteria are antibiotic use, major dietary changes within 4 weeks before the study, presence of a diagnosed clinically relevant medical condition (e.g., Crohn’s disease, diagnosed eating or GI disorders), intake of significant concomitant medication (e.g., immunomodulating therapy, mesalazines), and pregnancy. No concurrent participation in other clinical trials investigating or potentially affecting GI health is allowed. Non-adherence to the supplementation, defined by missing >25% of supplement doses, can lead to exclusion from the trial at the investigator’s discretion.

Potential participants are recruited by distributing the study information and a flyer within the networks of the Swiss Paraplegic Association, the Swiss Paraplegic Centre, and the Swiss Paraplegic Research. In the case of a low recruitment rate, study information will also be spread through community platforms, both online and in magazines (e.g., Paracontact). Interested participants are contacted by phone or in person to perform the screening, where eligibility criteria are assessed, and the participant is informed about the study and what procedures it entails. Written participant information and an informed consent form are provided. After at least 24 h of consideration time, informed consent will be obtained from each participant.

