### 2.4. Assessments

Outcome data are gathered at four timepoints: baseline (T1), after the first eight-week intervention phase (T2), after the four-week washout (T3), and after the second intervention phase (T4) - an overview can be found in Table 1. The primary endpoint is the GIQLI, indicating changes in subjective GI health [45]. The GIQLI is a questionnaire consisting of 36 questions assessing health-related quality of life in GI disorders, each on a scale from 0 to 4 [46]. It captures a person’s own perception of symptoms, functional limitations, and the psychosocial impact thereof. The GIQLI can range from a score of 0 to 144, with higher scores indicating better gut health and satisfaction with gut health.

Secondary endpoints cover gastrointestinal transit, systemic and mucosal biology, and safety. GITT is measured in the home setting with the Blue Dye Method, defined as the interval between ingestion of blue food coloring on an empty stomach and the first and last appearance of blue-colored stool [47,48]. Blood serum collected at each visit is analyzed with the Olink Target 48 Cytokine panel (Olink Proteomics AB, Uppsala, Sweden), which quantifies 45 inflammation-related proteins, including cytokines and chemokines such as IL-2 and TNF-α. These markers have been shown to be elevated in the serum of individuals with chronic SCI patients compared to healthy controls [49]. Fecal microbial community structure is characterized by full-length 16S rRNA gene sequencing on the MinION Nanopore sequencer (Oxford Nanopore Technologies, Oxford, UK). DNA is extracted with the QIAamp PowerFecal Pro DNA kit (QIAGEN, Hilden, Germany) using ten-minute bead-beating with 0.1 mm zirconia beads, quantified with Qubit™ 4.0 dsDNA HS fluorimeter (Thermo Fisher Scientific, Waltham, MA, USA), and prepared with the MinION Nanopore Ligation Sequencing Kit (SQK-LSK114) plus native barcodes (EXP-PBC096) (Oxford Nanopore Technologies, Oxford, UK). Libraries are pooled equimolarly, loaded on R10.4.1 flow cells, and base-called with Dorado; reads below a quality score of 9 are discarded. Emu assigns taxonomy. Supplement tolerance and all adverse events are documented throughout the study.

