## 3. Data Analyses

An intention-to-treat analysis will be conducted to minimize potential bias resulting from disruption to baseline equivalence following randomization, which may occur due to participant withdrawal, non-adherence to the study protocol, or excessive missing data. Participants will be included in analyses only where data are available. Protocol deviations, early withdrawals, and loss to follow-up will be documented and evaluated. Basic univariable statistical analysis techniques will be used to describe the study population as well as the primary and secondary outcomes at the different measurement points. To evaluate the longitudinal variation in the primary outcome and secondary outcomes, we will use multilevel mixed-effects models that appropriately account for the within- and between-individual sources of variance in outcome variation. In these models, participants are treated as random effects, while intervention and period are used as fixed effects. All models will be adjusted for the baseline value of the respective outcome measured before each period. To evaluate potential carryover effects, sequence (AB vs. BA) will be included as a fixed effect, and treatment-by-period interactions will be tested. Furthermore, pre-period baselines will be compared to verify that the gut environment returned to its SCI-baseline during washout, and a carryover term will be incorporated into the model to identify residual effects. If significant carryover is detected, a sensitivity analysis using only period 1 data will be performed to provide an unbiased estimate of the intervention effect. Depending on the findings, subgroup analyses may be performed for personal parameters (e.g., sex, lesion level). For the microbiome analyses, diversity indices will be compared using paired *t*-tests while correcting for multiple testing using the Benjamini–Hochberg method. A significance level of 5% will be applied. Protein concentrations will be reported as absolute abundances in pg/mL. Absolute abundance will be tested with mixed-effects models analogous to the primary analysis. The Benjamini–Hochberg procedure will control the false-discovery rate at 5%. Multi-omics integration will employ sparse partial least-squares regression to relate inflammatory proteins, microbial genera, and clinical outcomes (GIQLI, GITT). Statistical software packages to be used include R (Version 4.5.2), Stata (Version 19.0), and SPSS (Version 31.0), or any newer stable version available at the time of data analysis.

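### Adjusting every mixed model for the pre-period value on available data only drops an observed T4 (or, for transit time and serum proteins, T2) when T3 (or T1) is missing

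*Protocol article*

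**What the plan says.** Section 3 (Data Analyses) uses multilevel mixed models for the primary and secondary outcomes, in which "participants are treated as random effects, while intervention and period are used as fixed effects". It then adds that "All models will be adjusted for the baseline value of the respective outcome measured before each period". The covariate is therefore T1 for the period ending at T2, and T3 for the period ending at T4. Serum proteins are to be modelled in the same way as the primary outcome.

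On missing data the section says: "Participants will be included in analyses only where data are available". The population is described thus: "An intention-to-treat analysis will be conducted to minimize potential bias resulting from disruption to baseline equivalence following randomization". Excessive missing data is among the causes of that disruption which the section lists.

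Two other statements limit the point. Section 2.2 admits people with "a GIQLI score below 110 at baseline (T1), are included", so every included participant has a T1 GIQLI. For the microbiome, Section 3 says that "diversity indices will be compared using paired *t*-tests", with no baseline covariate mentioned.

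**The concern.** A regression row can be used only if its outcome and all its covariates are present. With the pre-period value as a covariate and an available-data rule, a measured T4 without a T3 is not used, and neither is a measured T2 without a T1. The value lost is a post-randomisation outcome that was observed, and the reason for losing it is a gap in an adjustment variable. That sits poorly with an intention-to-treat label adopted to limit the effect of missing data. It also gives up the within-person comparison that Section 4 calls the clear strength of the design.

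Exposure differs by outcome. GIQLI is a questionnaire completed at the study-centre visit (Table 1), and only T3 can be missing. Transit time is collected at home at four occasions, and it ends only with the last blue stool, in a population that Section 4 says has prolonged transit. One missed T3 blood sample removes the T4 row from the models of all 45 proteins.

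**Working it through.** **1. Do the two rules drop observed outcomes?** A 50-person two-period crossover was simulated with all 100 outcomes observed and 5 T3 covariates set missing. The mixed model with supplement, period, sequence and pre-period value used 95 rows. All 50 persons still contributed, but complete pairs fell from 50 to 45.

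**2. Which outcomes are exposed?**
- GIQLI: T3 only, because T1 is an entry criterion (Section 2.2).
- Transit time and serum proteins: T1 and T3.
- Diversity indices: not exposed, because they are compared by paired t-tests.
- Withdrawal before T4: not counted, because that pair is lost under any rule.

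**3. What is a broken pair worth?** Let ρ be the within-person correlation of the modelled outcomes and SDd the SD of the within-person difference. With balanced sequences, a complete pair gives information 1/SDd² on the supplement effect, and a single row gives (1 − ρ)/2 of that. With P pairs and K single rows out of 50 persons:

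SE ratio = √(50 / [P + K(1 − ρ)/2])

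The missingness rates and ρ are assumptions, since the article gives neither. Missing values at T1 and T3 are taken as independent.

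| Missing, with outcomes observed | P | K | ρ = 0.3 | ρ = 0.5 | ρ = 0.7 |
|---|---|---|---|---|---|
| 5% of T3 | 47.5 | 2.5 | 1.017 | 1.019 | 1.022 |
| 10% of T3 | 45 | 5 | 1.034 | 1.040 | 1.045 |
| 20% of T3 | 40 | 10 | 1.072 | 1.085 | 1.098 |
| 10% of T1 and of T3 | 50 × 0.9² = 40.5 | 50 × 2 × 0.9 × 0.1 = 9 | 1.070 | 1.082 | 1.093 |
| 20% of T1 and of T3 | 50 × 0.8² = 32 | 50 × 2 × 0.8 × 0.2 = 16 | 1.153 | 1.179 | 1.206 |

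Example: 10% of T3 missing and ρ = 0.5 gives √(50 / (45 + 5 × 0.25)) = √(50/46.25) = 1.040.

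The formula leaves out the baseline covariate itself. Adjusting for it lowers the remaining within-person correlation, so the left-hand column is the nearer guide. Simulations that include the covariate (50 persons, correlation 0.5 or 0.7 between visits, complete outcomes), compared with complete baselines, gave about 3-4% for 10% of T3, 6-9% for 10% of both, and about 16% for 20% of both. Using the participant's other untreated value as the covariate recovered the loss.

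**4. What does it mean for GIQLI power?** Section 2.1 gives 50 participants, 5% significance and 85% power, "applying a clinically relevant mean difference of 10 points on the GIQLI". The SD is not printed, so 50 cannot be reproduced, only solved backwards. Assuming a two-sided test, SDd = 10 × √50 / (1.960 + 1.036) = 23.6, so the full-data SE is 23.6/√50 = 3.337. Power = Φ(10/SE − 1.960).
- Full data: Φ(2.996 − 1.960) = 85.0%.
- 5% of T3 missing: SE 3.393 to 3.411, power 83.8% to 83.4%.
- 10% of T3 missing: SE 3.451 to 3.489, power 82.6% to 81.8%.
- 20% of T3 missing: SE 3.578 to 3.663, power 79.8% to 77.9%.

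**The case against.** The strongest reply is that the article nowhere says an outcome is discarded when its baseline is absent. The available-data sentence speaks of participants, and the handling of a missing covariate is commonly left to an analysis plan, which is not shown here. That stands in part: the lack of a covariate rule is not in itself a fault. But both rules are printed, and a mixed model fitted by them loses these rows unless a further rule is added.

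A reader might also infer more than the documents support:
- *Randomised people are excluded, or four complete values per person are required.* Someone with one missing baseline normally keeps the other period's row. That row is not worthless: by the formula above it carries (1 − ρ)/2 of a pair's information, or 15% to 35% for ρ from 0.7 to 0.3.
- *A missing T1 harms the primary analysis.* It cannot arise for GIQLI.
- *A missed stool sample at T3 removes the T4 diversity value.* The stated paired t-tests carry no covariate.
- *The loss is selective and biases the result.* People with slow transit are plausible candidates for an incomplete T3 reading. However, dropping rows because of the covariate's own value need not bias the supplement effect. In a simulation that removed the highest 5% or 10% of T3 values, bias stayed below 0.005 SD, as with full data.

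Finally, adjusting a crossover model for period baselines is a recognised choice. That also stands: the objection here is to the rows it loses, not to the adjustment.

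**Conclusion.** The point holds as a limited, avoidable loss of precision that follows from two printed rules. It concerns T3 for GIQLI, and T1 and T3 for transit time and serum proteins, and only where the later outcome was observed. At an assumed 10% of T3 missing, the standard error rises by about 3-4%, which for GIQLI is roughly 2 to 3 power points on the back-solved SD. With 10% of both baselines missing the rise is about 6-9%, and with 20% of both about 16%.

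These sizes rest on assumed missingness rates, assumed correlations of 0.3 to 0.7 and independent gaps. If T3 attendance is nearly complete, the effect on GIQLI is negligible. Bias is not demonstrated. The point is minor for the primary outcome and more relevant for the secondary outcomes that need a successful collection at each of four occasions.

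**What to change.** State in Section 3, or in the analysis plan, that no observed T2 or T4 value is dropped because its pre-period value is missing. Define the analysis set as all randomised participants with at least one T2 or T4 value. Then choose one of these:

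1. Fit T1-T4 jointly as responses, with visit means, a supplement effect at T2 and T4, and a within-person covariance. A missing T1 or T3 is then handled by the likelihood.
2. More simply, keep the present model and use the participant's other untreated value (T1 for T3, or T3 for T1) when one is missing. A participant lacking both would still lose the rows, so the first option meets the stated rule more fully.

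The cost is a sentence or two and a changed model call; no new data are needed, and data collection is planned to run to summer 2027. The joint model relies on missing-at-random and estimates a somewhat larger covariance structure from 50 people, repeated for 45 proteins. Missing-at-random would not hold if a T3 transit reading were absent because of its own value. The substitution assumes a completed washout, which the plan itself sets out to test.

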The study is subject to several limitations. The open-label nature of the study might introduce a potential bias. With the probiotic packaging resembling a medicinal product, versus the prebiotic clearly coming from a grocery store, participants may have different expectations for the efficacy of either supplement, which may bias their responses. This is not preventable, given the need for specific packaging for both supplements. Additionally, as diet and lifestyle are not strictly controlled, microbiome changes may be confounded, which in a real-life setting cannot be avoided. Despite not being controlled, by assessing physical activity and nutrition at each timepoint, big lifestyle changes can be detected and taken into consideration when analyzing the data. Further, at home supplementation makes strict control of adherence impossible; however, by asking participants to return empty packages after the intervention period, a sense of control is added and quantification of adherence is possible.

Another potential limitation of this crossover design is the risk of carryover effects, where the physiological and microbial changes from the first intervention might persist into the second period. Given the neurogenic bowel dysfunction inherent in SCI, transit times are prolonged, which could theoretically extend the influence of interventions. However, this risk is mitigated by the implementation of a 4-week washout period, exceeding the 2-week window typically required for the microbiome to revert to baseline after a dietary perturbation, and by employing a rigorous four-tiered statistical framework to detect sequence and period interactions [57,58,59,60].

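### Sequence, treatment-by-period and carryover are one contrast in this two-period design, and the protocol does not say which fit gives the primary estimate

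*Protocol article*

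**What the plan says.** Section 2.1 describes a crossover with two sequences and two 8-week periods, where "a sample size of 50 participants, with 25 participants in each group, was determined".

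Section 3 starts from a mixed model with participant as a random effect and intervention and period as fixed effects, adjusted for the outcome value before each period. For carryover it then lists four things:

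- "sequence (AB vs. BA) will be included as a fixed effect, and treatment-by-period interactions will be tested" (two of the four);
- "pre-period baselines will be compared to verify that the gut environment returned to its SCI-baseline during washout";
- "a carryover term will be incorporated into the model to identify residual effects".

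A significant carryover result triggers an analysis of period 1 alone, labelled a sensitivity analysis and described as unbiased. Section 4 says that the carryover risk is mitigated by the washout and "by employing a rigorous four-tiered statistical framework to detect sequence and period interactions".

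Section 2.2 is also relevant to the baseline check: participants with "a GIQLI score below 110 at baseline (T1), are included".

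**The concern.** A crossover with two sequences and two periods has very little room for carryover terms. Once intervention and period are in the model, one fixed parameter is left. The protocol asks for three terms in that one place and counts them as separate safeguards.

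Two things are at stake. First, the protection against carryover claimed in Section 4 is larger than the design can give. Second, the choice of extra term can change what the intervention coefficient estimates. If redundant terms are entered together, software drops some by order or coding, and the reported effect may be a within-person or a between-person comparison depending on which one goes.

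There is a secondary issue. If the baseline check compares T3 with T1 for the GIQLI, T1 was selected to be low and T3 was not, so T3 can rise without any carryover.

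**Working it through.** **1. Rank.** Inputs: two sequences, two periods, T2 and T4 as responses, T1 and T3 as covariates (Sections 2.1 and 3). Code T = 1 for treatment A, P = 1 for period 2, S = 1 for sequence BA, and C = 1 for residual A in period 2.

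| Cell | 1 | T | P | S | T×P | C |
|---|---|---|---|---|---|---|
| AB, period 1 | 1 | 1 | 0 | 0 | 0 | 0 |
| AB, period 2 | 1 | 0 | 1 | 0 | 0 | 1 |
| BA, period 1 | 1 | 0 | 0 | 1 | 0 | 0 |
| BA, period 2 | 1 | 1 | 1 | 1 | 1 | 0 |

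Two identities hold in every row: C = P − T×P, and S = 1 − T − P + 2(T×P). Intercept, T and P have rank 3. Any one added term gives rank 4. Any two give 5 columns at rank 4, and all three give 6 columns at rank 4. A participant-level baseline covariate does not remove these identities. Each added term estimates a multiple of (1, 1, −1, −1) over AB1, AB2, BA1, BA2, which is a between-person comparison.

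**2. What the intervention coefficient estimates** (weights over AB1, AB2, BA1, BA2):

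- no extra term, sequence, or an effect-coded interaction: (0.5, −0.5, −0.5, 0.5), the crossover estimate;
- carryover, or a reference-coded interaction: (1, 0, −1, 0), the period-1 difference.

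Simulation of the mixed model (800 runs per setting) confirms this. Without the baseline covariate, the estimate with a carryover term equals the period-1 difference to machine precision. With the covariate it follows the period-1 ANCOVA closely (correlation 0.99) but not exactly, because the common baseline slope borrows a little from period 2.

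**3. Power.** The plan gives 10 points, 5%, 85% and N = 50, but no SD or correlation, so N cannot be reproduced. The SD was solved for under two assumptions, with a two-sided test.

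*Crossover formula.* Normal approximation: SD of differences = 10·√50/(1.96 + 1.036) = 23.6; with a t-test, 23.1. Between-person SD = 23.1/√(2(1−ρ)). T1 adjustment multiplies it by √(1−ρ²), taking ρ for T1-T2 as well. Power uses the noncentral t for 25 v 25, with noncentrality 10/(SD·√(2/25)).

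| ρ | SD | Adjusted SD | Period-1 power, unadjusted | Period-1 power, T1-adjusted |
|---|---|---|---|---|
| 0.5 | 23.1 | 20.0 | 32% | 41% |
| 0.7 | 29.8 | 21.3 | 21% | 37% |
| 0.8 | 36.5 | 21.9 | 16% | 35% |

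The plan adjusts for baseline, so the last column applies. The fair comparator is the baseline-adjusted crossover fit, which in the simulation (SD of differences 23.6) had about 78% power at ρ = 0.5 and 73% at 0.7.

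*Two-sample formula.* SD = 10/(√(2/25)·(1.96 + 1.036)) = 11.8, slightly less with a t-test. At SD 11.7 the period-1 comparison has 84% power unadjusted, and more with adjustment.

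**4. Regression to the mean in T3 against T1.** Expected rise after full washout = (1−r)·SD·φ(z)/Φ(z), with z = (110 − mean)/SD. Mean, SD and r refer to the population before the cut-off and are assumptions.

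- Mean 80, SD 15, r 0.8: z = 2, giving 0.2 × 15 × 0.055 = 0.2 points.
- Mean 110, SD 20, r 0.7: z = 0, giving 0.3 × 20 × 0.798 = 4.8 points.

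The range is 0.2-1.2 points at a mean of 80-85 and 0.9-4.8 at 95-110.

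**The case against.** Section 3 can be read as a base model that gives the effect, followed by diagnostic fits for carryover. It introduces the extra terms for that purpose, says that the interaction is tested, and labels the period-1 analysis as sensitivity. On that reading the primary estimate stays within-person. This stands. A reader might infer that the plan makes the primary result a period-1-only comparison, but the documents do not say so. They leave it open which fit is primary, and the wording that puts the carryover term into the model does not settle it.

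A reader might also infer a collapse in power from 85% to between 16% and 32%. That is not supported either. Those figures leave out the planned baseline adjustment and rest on one back-solved SD. The implied between-person SD of 23 to 37 is well above the 15-20 assumed for the regression-to-the-mean range. With SD 15-20 and correlation 0.7-0.8, T1-adjusted period-1 power is 68-97%.

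The baseline comparison is a separate, identifiable check. If T1 to T4 were all modelled as responses, the eight cell means would support eight parameters (rank 8), and sequence, carryover at T3 and a period-2 carryover or interaction term could be separated. Section 3, however, uses T1 and T3 as covariates.

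On regression to the mean, Section 3 refers to the gut environment, where selection on GIQLI matters far less, and does not say whether baselines are compared within person or between sequences. Candidates must also report significant complaints at screening, so their mean may lie well below 110 and the shift may be small. The point is therefore conditional and secondary.

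**Conclusion.** The identifiability point holds and needs no assumed figure. Sequence, treatment-by-period and carryover are one between-person contrast in the model as described. They cannot be fitted together, and the four-tier claim in Section 4 amounts to that contrast plus a baseline comparison.

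The primary estimate is not clearly fixed. It loses the within-person comparison only if the carryover term or a reference-coded interaction is kept in the fit that is reported. In that case baseline-adjusted power for 10 points is about 35-41% if N = 50 came from a crossover formula (SD of differences about 23, correlation 0.5-0.8), and about 84% or more if it came from a two-sample formula (SD about 11.7). The protocol does not say which was used.

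A T3-against-T1 check on the GIQLI could show a rise of about 0.2-4.8 points after full washout, for an assumed unselected mean of 80-110, SD 15-20 and correlation 0.7-0.8. That this would commonly be mistaken for failed washout cannot be concluded from the documents.

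**What to change.** - Name the primary model: intervention and period (sequence optional), a random participant effect and the planned baseline adjustment, with no carryover or treatment-by-period term.
- State that sequence, treatment-by-period and carryover are the same contrast here, and report it once, with its 95% CI, as descriptive.
- Do not let its significance decide whether the period-1 analysis is done. The contrast contains the period-1 difference, so an estimate reported only after a significant result cannot be called unbiased. Report the period-1 analysis unconditionally as a sensitivity analysis, or drop it.
- For the GIQLI, compare T3 between the two sequences, adjusted for T1, with a CI. Selection on T1 affects both sequences alike.
- Delete the four-tier description in Section 4.

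The cost is a few sentences and a more modest claim about carryover detection. No change to data collection or sample size is needed.

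### For GIQLI, checking washout by T3 against T1 is shifted upward by regression to the mean, because entry requires a T1 score below 110 and T3 is unselected

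*Protocol article*

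**What the plan says.** Section 2.2 (Study Participants) sets two entry hurdles on GI complaints: a yes at screening, and a score threshold on the primary outcome, "a GIQLI score below 110 at baseline (T1". The T1 score is therefore both an entry filter and the period 1 baseline. T3, taken after washout, is the period 2 baseline. Neither section 2.4 nor Table 1 gives it a score threshold.

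Section 3 (Data Analyses) lists several carryover checks. One is that "pre-period baselines will be compared to verify that the gut environment returned to its SCI-baseline during washout". The others are that "sequence (AB vs. BA) will be included as a fixed effect, and treatment-by-period interactions will be tested", and that "a carryover term will be incorporated into the model to identify residual effects". The stated consequence is: "If significant carryover is detected, a sensitivity analysis using only period 1 data will be performed".

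For the baseline comparison, the article does not name the test, the outcomes covered, or whether it is made across all participants, within sequence or between sequences. It states no equivalence margin and does not mention regression to the mean.

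**The concern.** A return to baseline is a change over time, so the natural reading of the check is T3 against T1. For GIQLI this is not a fair comparison. People who score low at T1 partly by chance pass the filter, and those who score high by chance are turned away. At T3 the chance component is no longer selected, so the mean is expected to rise.

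Two further problems follow.

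- A shift from T1 to T3 common to both sequences mixes regression to the mean, time trend and any residual effect shared by the two supplements. The period effect absorbs it. What threatens the probiotic–prebiotic contrast is a residual effect that differs between sequences, and a pooled T3–T1 comparison does not target that.
- A non-significant difference is not evidence of return, least of all without a margin.

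At stake is the washout conclusion for the primary outcome, and possibly whether the period 1 sensitivity analysis is run. That analysis would compare 25 with 25 people and give up the within-person comparison that section 4 names as the design's strength. The check carries some weight, because the washout evidence cited in section 2.3 concerns inulin-type fructans in non-disabled people, not the probiotic.

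**Working it through.** **Inputs from the article.** Threshold 110 at T1 (section 2.2); 50 participants, 25 per sequence; 5% level; relevant difference 10 points (section 2.1). The plan gives no figure for the T1–T3 comparison that could be reproduced, and the SD behind the sample size is not stated.

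**Assumed, not in the article.** GIQLI before the filter is normal with mean μ of 90–110 and SD σ of 15–20; T1–T3 correlation ρ is 0.5–0.9; there is no carryover and no time trend.

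**Shift from selection.** With k = (110 − μ)/σ and λ = φ(k)/Φ(k):

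- E[T1 | T1 < 110] = μ − σλ
- E[T3 − T1 | T1 < 110] = (1 − ρ)σλ
- Var(T3 − T1) = (1 − ρ)²σ²(1 − kλ − λ²) + σ²(1 − ρ²)

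Example, μ = 100, σ = 20: k = 0.5, λ = 0.352/0.691 = 0.509, σλ = 10.2, so the mean T1 among those admitted is 89.8. The shift is 0.3 × 10.2 = 3.05 points at ρ = 0.7 and 0.2 × 10.2 = 2.04 at ρ = 0.8.

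**False rejection.** Two-sided 5% paired t-test on all 50, from the noncentral t with noncentrality shift × √50 / SD of change:

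| Mean | SD | ρ | Shift | SD of change | False rejection |
|---|---|---|---|---|---|
| 90 | 15 | 0.9 | 0.27 | 6.66 | 5.9% |
| 90 | 20 | 0.7 | 1.73 | 15.06 | 12.5% |
| 100 | 15 | 0.8 | 1.28 | 9.26 | 16.0% |
| 100 | 20 | 0.8 | 2.04 | 12.32 | 20.9% |
| 100 | 20 | 0.7 | 3.05 | 14.88 | 29.6% |
| 110 | 20 | 0.7 | 4.79 | 14.73 | 61.5% |
| 110 | 20 | 0.5 | 7.98 | 18.34 | 85.4% |

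The first and last rows are the ends of the full grid.

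**Which comparison sees what.** Rejection rates from 20,000 simulated trials in each of three cases with SD 20 (mean 100, ρ 0.8; mean 100, ρ 0.7; mean 90, ρ 0.8). The between-sequence test here compares T3 − T1, 25 against 25:

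| Residual effect in the two sequences | Pooled T3 vs T1 | Between sequences |
|---|---|---|
| 0 and 0 | 10–30% | 5% |
| +5 and +5 | 93–98% | 5% |
| +5 and −5 | 8–26% | 64–80% |
| +5 and 0 | 51–72% | 22–29% |
| −2.5 and −2.5 | 6–12% | 5% |

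The last row shows masking: at mean 100, ρ 0.8, a true worsening of 2.5 points in both sequences appears as a mean change of about −0.5, with 6% rejection.

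**Outcomes not selected at T1.** The shift in SD units is (correlation with GIQLI) × (1 − ρ) × λ. At mean 100, SD 20, ρ = 0.7 this is 0 for no correlation, 0.2 × 0.3 × 0.509 = 0.03 for 0.2, and 0.3 × 0.3 × 0.509 = 0.05 for 0.3.

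**The case against.** The strongest reply is that the article says only that the baselines will be compared. It does not plan a pooled paired test of GIQLI; the only paired t-tests it names are for microbiome diversity indices. A between-sequence comparison would be free of this bias, and a condensed article may leave the form to a fuller document. This stands in part: the rejection rates above describe one natural implementation, not a stated one. But the stated purpose is to show a return, which a between-sequence comparison cannot do, and any T3-against-T1 comparison of GIQLI carries the shift, whether pooled or within sequence.

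Second, the sentence speaks of the gut environment, and stool, serum and transit measures are not filtered at T1. This stands, and the point is limited to GIQLI.

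Third, T3 against T1 does address return to baseline, and the sequence, treatment-by-period and carryover terms are planned to protect the contrast. Adjusting each model for its pre-period baseline also takes up part of any T3 difference. This stands too, although those three terms largely overlap in a two-treatment, two-period design and do not repair the T1–T3 comparison.

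Fourth, the larger figures need a high pre-selection mean. At mean 110 half of those reaching T1 would fail the filter, although they have already reported significant complaints. At mean 90, false rejection is only 6–18%. This also stands: the upper end of the range should not be taken as the expected size.

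A reader might infer that the primary treatment effect is biased. The documents do not support that. Allocation is randomised, so the selection shift is equal in expectation in both sequences and falls into the period effect. Nor does the article say that the baseline comparison alone triggers the period 1 analysis, or that this analysis replaces the main one; it is called a sensitivity analysis.

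**Conclusion.** The point holds for GIQLI. The direction of the shift follows from the entry rule and any T1–T3 correlation below 1. Its size cannot be derived from the article: over the assumed range it is 0.3 to 8.0 points, with 6% to 85% false rejection by a pooled paired test on 50 people. The middle case (mean 100, SD 20, correlation 0.7–0.8) gives 2.0–3.1 points and 21–30%, four to six times the nominal 5%.

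What is affected is the washout and carryover conclusion for GIQLI, in either direction, and possibly the decision to run the period 1 analysis. It is a correction worth making to the wording and method of one check, not a threat to the main result.

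**What to change.** In section 3, or in the analysis plan, separate the two questions for GIQLI. Possible wording:

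> For GIQLI, differential carryover at the start of period 2 will be estimated as the difference in T3 between sequences, adjusted for T1, with a 95% confidence interval. The change from T1 to T3 will be described only. Because entry required a T1 score below 110, a rise is expected from regression to the mean. These comparisons explore, and do not verify, return to baseline.

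The interval is best read against a margin fixed in advance rather than by a significance test. The article should also say whether the baseline comparison counts towards the finding of significant carryover that leads to the period 1 analysis.

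The cost is a change of wording and one ANCOVA on data already collected. The selection shift cancels between randomised sequences. The drawback is precision: at SD 20 and correlation 0.7 the half-width is 20 × √(1 − 0.7²) × √(2/25) × 2.01 = 8.1 points, close to the 10-point relevant difference. This comparison therefore cannot prove complete washout either, and the report should say so.
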